# Protocol for pilot cluster RCT of project respect: a school-based intervention to prevent dating and relationship violence and address health inequalities among young people

**DOI:** 10.1186/s40814-019-0391-z

**Published:** 2019-01-22

**Keywords:** Dating and relationship violence, Violence prevention, School intervention, Cluster randomised trial, Realist evaluation, Process evaluation, Adolescent

## Abstract

**Background:**

Dating and relationship violence (DRV)—intimate partner violence during adolescence—encompasses physical, sexual and emotional abuse. DRV is associated with a range of adverse health outcomes including injuries, sexually transmitted infections, adolescent pregnancy and mental health issues. Experiencing DRV also predicts both victimisation and perpetration of partner violence in adulthood.

Prevention targeting early adolescence is important because this is when dating behaviours begin, behavioural norms become established and DRV starts to manifest. Despite high rates of DRV victimisation in England, from 22 to 48% among girls and 12 to 27% among boys ages 14–17 who report intimate relationships, no RCTs of DRV prevention programmes have taken place in the UK. Informed by two school-based interventions that have shown promising results in RCTs in the USA—Safe Dates and Shifting Boundaries—Project Respect aims to optimise and pilot a DRV prevention programme for secondary schools in England.

**Methods:**

Design: optimisation and pilot cluster RCT. Trial will include a process evaluation and assess the feasibility of conducting a phase III RCT with embedded economic evaluation. Cognitive interviewing will inform survey development.

Participants: optimisation involves four schools and pilot RCT involves six (four intervention, two control). All are secondary schools in England. Baseline surveys conducted with students in years 8 and 9 (ages 12–14). Follow-up surveys conducted with the same cohort, 16 months post-baseline. Optimisation sessions to inform intervention and research methods will involve consultations with stakeholders, including young people.

Intervention: school staff training, including guidance on reviewing school policies and addressing ‘hotspots’ for DRV and gender-based harassment; information for parents; informing students of a help-seeking app; and a classroom curriculum for students in years 9 and 10, including a student-led campaign.

Primary outcome: the primary outcome of the pilot RCT will be whether progression to a phase III RCT is justified. Testing within the pilot will also determine which of two existing scales is optimal for assessing DRV victimisation and perpetration in a phase III RCT.

**Discussion:**

This will be the first RCT of an intervention to prevent DRV in the UK. If findings indicate feasibility and acceptability, we will undertake planning for a phase III RCT of effectiveness.

**Trial registration:**

ISRCTN, ISRCTN 65324176. Registered 8 June 2017.

**Electronic supplementary material:**

The online version of this article (10.1186/s40814-019-0391-z) contains supplementary material, which is available to authorized users.

## Background

### Dating violence and public health

Dating and relationship violence (DRV)—used to describe intimate partner violence during adolescence [1–3]—encompasses threats, emotional abuse, controlling behaviours, physical violence and coerced, non-consensual or abusive sexual activities perpetrated by a partner [4]. Globally, 30% of ever-partnered women report violence from current or previous partners at some point in their lives [5, 6]. Evidence suggests that partner violence begins early, with prevalence of DRV victimisation already reaching 29.4% among girls ages 15–19 [6–10]. Norms accepting of gender-based violence and harassment strongly correlate with DRV perpetration and victimisation [9–13] and young people identify concerns about social repercussions as a barrier to intervening in DRV as a bystander [14]. Young people who experience DRV are more likely to be victims or perpetrators of relationship violence as adults [15–17]. Early experience of DRV is also associated with subsequent adverse outcomes such as substance misuse and anti-social behaviour [18–20], sexually transmitted infections (STIs) and teenage pregnancy [21], eating disorders [17], suicidal behaviours and other mental health problems [17, 22], physical injuries [23] and low educational attainment [22]. Experiencing violence during pregnancy correlates with poorer maternal and neonatal health outcomes [21, 24]. In addition to its harms, domestic violence is associated with significant financial costs to health systems. In 2008 in the UK, it was estimated that domestic violence cost the National Health Service £1.73 billion per year with total costs to the UK economy of £15.73 billion per year [25].

### Rationale for proposed study

There is a pressing need to prevent DRV in the UK. Recent surveys of English young people suggest victimisation prevalence of 22–48% for young women and 12–27% for young men aged 14–17 years who report an intimate relationship [26–28]. Universal, primary prevention of DRV is required since these behaviours are widespread and under-reported [29]. Prevention during early adolescence is important because this is the time when dating behaviours begin, behavioural norms become established and DRV starts to manifest [30, 31]. Schools are a key site to achieve this since they are settings in which young people are socialised into gender norms and in which significant amounts of gender-based harassment and DRV go unchallenged [32, 33]. Because DRV arises not only from individual deficits in communication and anger management skills [34] but also from sexist gender norms and pervasive gender-based harassment [23, 35–37], within schools multi-component interventions—for example, addressing school curricula, policies and environments—are required [38] to address factors driving DRV at multiple levels of the social ecology.

There is thus a pressing need for a UK-based randomised controlled trial (RCT) of a universal multi-component, school-based prevention intervention, informed by existing evidence, which targets early adolescents. Project Respect aims to meet this need. The Project Respect intervention is designed to address similar topics to those targeted by the effective Safe Dates [39] and Shifting Boundaries interventions [40]. The programme’s theory of change outlines hypothesised pathways to programme outcomes. There is a need for a UK-specific intervention because given cultural differences, direct replication of a US intervention is unlikely to be effective in the UK [41]. We will therefore begin by working with UK secondary school staff and students to elaborate and optimise the intervention and produce the manual, curriculum and other intervention materials. We will then subject Project Respect to a pilot cluster RCT to assess feasibility and acceptability and optimise methods prior to a phase III RCT. This will be the first UK RCT of an intervention to prevent DRV among young people.

### Interventions

Guidance on domestic violence published by the UK National Institute for Health and Care Excellence in 2014 has highlighted the lack of current evidence for interventions preventing adolescent DRV [42]. Recent Cochrane and Campbell reviews of DRV prevention have conducted meta-analyses to estimate effects on behavioural, attitudinal and knowledge outcomes, finding overall effects on knowledge and attitude, but not behaviour [43, 44]. However, more promising results for behaviour are reported from RCTs of the Safe Dates and Shifting Boundaries interventions [39, 40]. These were included in the Campbell but excluded from the Cochrane review; exclusion of Safe Dates and Shifting Boundaries from the Cochrane review was due to incomplete reporting and recent publication respectively. The authors of the Cochrane review noted that non-inclusion of Safe Dates was a major limitation of their review. These interventions were also identified in a broader review of interventions to prevent sexual violence perpetration as the only effective interventions addressing this issue among young people [45].

The Safe Dates curriculum was delivered over ten sessions to eighth and ninth grade students (aged 13–15 years) in North Carolina, USA and focused on the consequences of DRV, gender roles, conflict management skills, norms, help-seeking and student participation in drama and poster activities. A school cluster RCT [39, 46] reported significantly reduced perpetration of physical DRV and victimisation of serious physical DRV (*p* < 0.05 for both) and significantly reduced perpetration and victimisation of sexual DRV (*p* = 0.04, *p* = 0.01 respectively) at 4-year follow-up. The duration of these effects suggests these might be real behavioural effects rather than merely social desirability effects on reporting. The intervention was equally effective for females and males [47].

A four-arm school cluster RCT of the Shifting Boundaries interventions allocated schools to receive one of the following: curriculum intervention, school environment intervention, combined intervention and neither intervention [40]. The curriculum comprised six sessions on the consequences of DRV, the social construction of gender roles and what constitutes healthy relationships. The environment intervention included higher levels of staff presence in hot-spots for gender-based harassment mapped by students, including use of joint faculty and student safety committees to help guide the placement of security personal, posters and increased sanctions for perpetrators including use of building-based temporary restraining orders and use of joint faculty-student safety committees. The environment-only and the combined interventions were effective in reducing sexual violence victimisation at 6-months follow-up (respectively OR = 0.662 *p* = 0.028; OR = 0.659 *p* = 0.011). There were also reductions in sexual violence perpetration in the environment-only and combined intervention (respectively OR = 0.527 *p* = 0.002; OR = 0.524 *p* = 0.001). There was no evidence of these effects with the curriculum-only intervention. Results show similar benefits for females and males and for those with and without a history of DRV [48]. The Cochrane review recommended that further research on multi-component interventions in schools is a priority. The Campbell review recommended that future interventions more explicitly address skills and the role of peer norms in preventing DRV.

### Benefits and risks

There are major potential public health benefits arising from the prevention of adolescent DRV, which affects a substantial proportion of young people in the UK. Components of the Project Respect intervention are similar to those comprising the effective Safe Dates and Shifting Boundaries interventions, which do not report physical or psychological harm stemming from such an intervention blending structural and curriculum components. Evidence suggests DRV research is unlikely to pose psychological risks to research participants [49]. Research participants will be informed that their participation in the research is voluntary and that they may withdraw at any point. As we cannot be certain prior to piloting that this intervention research poses no risk to participants, our process evaluation will explore potential for harm. Any potential mechanisms of harmful effects of the intervention will be explored through qualitative data in this pilot RCT and in later evaluation phases. We will closely liaise with participating schools to facilitate data collection with students. We will minimise disruption for staff and ensure student privacy and confidentiality both by employing strategies used successfully in our past work, such as having the trial manager liaise directly with each participating school to identify convenient times and places for data collection, and by piloting innovative methods in this context, such as the use of computer assisted self-interview (CASI) surveys. Ethical issues are discussed in more detail below.

## Methods

### Research aims, research questions and objectives

#### Aims

I.With stakeholders, to elaborate and optimise Project Respect, informed by existing research.II.To conduct a pilot RCT (four intervention, two control schools) in southern England.

#### Research questions

Is progression to a phase III RCT justified in terms of pre-specified criteria? These criteria are: randomisation occurs and four or more schools out of six accept randomisation and continue within the study; the intervention is implemented with fidelity in at least three of the four intervention schools; the process evaluation indicates the intervention is acceptable to 70% or more of year 9 and 10 students and staff involved in implementation; CASI surveys of students are acceptable and achieve response rates of at least 80% in four or more schools; and methods for economic evaluation in a phase III RCT are feasible.Which of two existing scales—the Safe Dates (SD) and the short Conflict in Adolescent Dating Relationships Inventory (CADRI-s)—is optimal for assessing DRV victimisation and perpetration as primary outcomes in a phase III RCT, judged in terms of completion, inter-item reliability and fit?What are likely response rates in a phase III RCT?Do the estimates of prevalence and intra-cluster correlation coefficient (ICC) of DRV derived from the literature look similar to those found in the UK so that they may inform a sample size calculation for a phase III RCT?Are secondary outcome and covariate measures reliable and what refinements are suggested?What refinements to the intervention are suggested by the process evaluation?What do qualitative data suggest about how contextual factors might influence implementation, receipt or mechanisms of action?Do qualitative data suggest any potential harms and how might these be reduced?What sexual health and violence-related activities occur in and around control schools?

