### Recruitment and randomisation

Four schools will be involved in intervention elaboration and optimisation, purposively sampled to vary by region and deprivation (as measured by the income deprivation affecting children index, IDACI). In the subsequent pilot RCT phase, three schools in southeast England and three schools in southwest England will be recruited; these schools will be different from those participating in optimisation. Schools taking part in the pilot RCT will be purposively sampled to ensure variation by deprivation and school-level value-added academic attainment, as approximate indicators of school capacity to deliver Project Respect.

We will recruit schools via letters and telephone calls to schools, local authorities, academy chains and school networks. Response rates will be recorded, as will any stated reasons for non-participation. After baseline CASI surveys with students at the end of years 8 and 9, schools will be stratified by region and randomly allocated 2:1 to intervention/control by the London School of Hygiene and Tropical Medicine (LSHTM) clinical trials unit (CTU). The 2:1 allocation will enable us to pilot randomisation while ensuring sufficient diversity among four schools for piloting the intervention. Retention of control schools will be maximised via £500 payment and feedback of survey data.

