We will survey absent students by leaving paper questionnaires and stamped addressed envelopes with their schools. When we conduct follow-up surveys 16 months post-baseline, with students who are near the beginning of years 10 and 11 (aged 14–15 and 15–16 years, respectively), we will collect self-report data on intervention participation, outcomes and potential mediators. Fieldworkers will be blind to school allocation. Based on past experience [84], in the pilot, we anticipate 95% baseline survey participation and 90% at follow-up. We will also conduct online staff surveys at baseline and 16 months post-baseline for the economic and process evaluations.

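### The retention and response progression criteria are pooled over arms, so the pilot's rule can be met with both control schools lost after randomisation

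*Protocol article*

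**What the plan says.** The Research questions section of the protocol article lists five progression criteria:

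1. Retention: "randomisation occurs and four or more schools out of six accept randomisation and continue within the study".
2. Fidelity: "the intervention is implemented with fidelity in at least three of the four intervention schools".
3. Acceptability: "the process evaluation indicates the intervention is acceptable to 70% or more of year 9 and 10 students and staff involved in implementation".
4. Survey: "CASI surveys of students are acceptable and achieve response rates of at least 80% in four or more schools".
5. Economics: "methods for economic evaluation in a phase III RCT are feasible".

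The Aims section fixes the arms: "To conduct a pilot RCT (four intervention, two control schools) in southern England". Under Outcome measures, the pilot's primary outcome is whether progression is justified by these criteria. Approach to data analysis adds one further condition: at least one of the two DRV scales must perform well, again with no mention of arm.

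Recruitment and randomisation treats control-school retention as something to be worked for: "Retention of control schools will be maximised via £500 payment and feedback of survey data".

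**The concern.** Criteria 1 and 4 both count to four, and there are exactly four intervention schools. Criteria 2 and 3 concern the intervention and those who receive or deliver it. Criterion 5 and the scale condition name no arm. Nothing written down therefore requires a control school to remain.

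The pilot is meant to show that a cluster trial can be run. Agreeing to be randomised is only part of that, because a school allocated to control must also stay and return follow-up surveys. If both control schools left after allocation, those two things would be undemonstrated, yet the rule as written could still be met. The protocol offers a payment and feedback to keep control schools, but no criterion tests whether they stayed.

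**Working it through.** **Inputs from the protocol article.** Four intervention and two control schools (Aims). Three schools in each of two regions, allocated 2:1 within region (Recruitment and randomisation). Retention threshold of four of six schools, and response threshold of 80% in four schools (Research questions). The article gives no school dropout rate, so every retention probability below is an assumption.

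**Step 1: reproduce the design.** Each region of three schools at 2:1 gives two intervention and one control. Two regions give 2 × 2 = 4 intervention and 2 × 1 = 2 control schools, as stated.

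**Step 2: list what passes criterion 1.** Let *i* (0 to 4) and *c* (0 to 2) be the intervention and control schools retained. The condition is *i* + *c* ≥ 4. The passing pairs (*i*, *c*) are (2,2), (3,1), (3,2), (4,0), (4,1) and (4,2). Counted school by school, 15 + 6 + 1 = 22 of the 2^6 = 64 patterns pass, and one of these has no control school.

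**Step 3: check (4,0) against the other criteria.** Four intervention schools can supply fidelity in three of four, acceptability among students and implementing staff, and 80% response in four schools. The economic criterion and the scale condition do not exclude (4,0).

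**Step 4: probability of passing criterion 1 with no control school.** With independent schools, retention *r_I* per intervention school and *r_C* per control school:

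P(4,0) = *r_I*^4 × (1 − *r_C*)^2

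Equal retention in both arms:

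| Assumed retention | P(4,0) |
|---|---|
| 0.50 | 0.0156 |
| 0.60 | 0.0207 |
| 0.70 | 0.0216 |
| 0.80 | 0.0164 |
| 0.90 | 0.0066 |
| 0.95 | 0.0020 |

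Preferential loss of control schools:

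- 95% intervention, 50% control: 0.95^4 × 0.5^2 = 0.8145 × 0.25 = 0.204.
- 95% intervention, 30% control: 0.8145 × 0.7^2 = 0.8145 × 0.49 = 0.399.

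**Step 5: effect of requiring at least one control school.** This removes (4,0) and nothing else. At 95% and 50%, the probability of passing criterion 1 falls from 0.947 to 0.743. The difference of 0.204 is the case with no control school left.

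**The case against.** The strongest reply is that this is a narrow drafting gap in a feasibility pilot. A vanished control arm would show in the planned flow chart of recruitment and response. The investigators' group and the Study Steering Committee monitor the criteria, all the research questions are meant to inform progression, and control schools are paid to stay. This lowers the chance that the gap would go unnoticed. It does not close it, because the article ties the decision to the pre-specified criteria and none of them refers to the control arm.

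Four stronger readings are tempting, and the documents do not support them.

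- *Comparator information would never be obtained.* Baseline surveys run in all six schools before randomisation, and the Comparator section has control-school provision examined at baseline. What would be lost is control follow-up and possibly the control-school interviews.
- *The survey criterion could be met on the baseline wave alone.* Criterion 4 names no wave, and under Assessment and follow up "we anticipate 95% baseline survey participation and 90% at follow-up". But it speaks of surveys in the plural, and the study has two student waves, so the natural reading covers both. Naming them is a clarification.
- *The chance of a false pass is simply the chance that both control schools leave.* At control dropout of 0.3 to 0.5 that chance is 0.3^2 = 9% to 0.5^2 = 25%. A pass in that case also needs all four intervention schools to stay. With the same dropout in both arms, the joint probability is 0.7^4 × 0.09 = 2.2% or 0.5^4 × 0.25 = 1.6%.
- *The fidelity criterion guarantees that three intervention schools are retained.* It concerns implementation. A school could deliver the programme and then miss the follow-up survey, so (2,2) stays among the pairs that pass on retention.

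**Conclusion.** The point holds as a defect in a stated decision rule. Criteria 1 and 4 can both be met by the intervention arm alone, no other stated condition needs a control school, and the rule is the pilot's primary outcome. That conclusion follows from the counts and rests on no assumption.

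How much it matters depends on why schools leave. If dropout is unrelated to arm, a pass on retention with no control school is rare, about 0.2% to 2.2% over assumed retention of 0.5 to 0.95. If control schools leave preferentially, which is the risk the £500 payment addresses, it becomes material: about 20% at assumed retention of 95% and 50%. These figures assume independent schools and use retention rates that the article does not give. They cover criterion 1 only, so the chance that every criterion is met with no control school can be no larger.

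This is an inexpensive improvement worth making. It does not undermine the pilot as a whole.

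**What to change.** Reword the two criteria along these lines:

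- Criterion 1: *at least four of the six schools, including at least one control school, accept randomisation and remain to the 16-month follow-up.*
- Criterion 4: *student CASI surveys are acceptable, with response of 80% or more at baseline and at the 16-month follow-up in at least four schools, including at least one control school.*

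Report retention and response by arm alongside the decision.

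No new data are needed. The cost is a slightly harder pair of criteria. One control school is a minimum chosen by judgement. With one control per region, it still allows a region to end without a control. Requiring both controls would avoid that, but would leave only (2,2), (3,2) and (4,2) as passing pairs on retention.

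Timing matters because this changes a pre-specified rule. Baseline enrolment began in June 2017, so 16 months falls at about October 2018, which is after submission in May 2018 but before publication in January 2019. The Study Steering Committee should agree the change before follow-up data are seen. If it is too late for that, the requirement should be reported openly as an added condition.
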